## **3.1. 3.1. Sample Size Calculation**

Considering the study by Braathen et al. (2008), which reported a variation in complete lesion response rates ranging from 64% to 91% after 3 months in the 8% (1 and 3 hours) and 16% (1 and 3 hours) groups, with a 95% confidence level and 80% power to detect differences between groups, the minimum sample size will be 36 participants per group, for a total of 144 participants. This result was obtained using a chi-square test for differences in proportions.

Figure 1 - Study Flowchart

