Wiegell et al. (2009) compared PDT mediated by MAL containing different concentrations (16% versus 8%) in participants with actinic keratosis in symmetrical areas of the face or scalp. In this study, the participants applied the product in the hospital and were instructed to expose themselves to sunlight for the remainder of the day. The average exposure time was 244 minutes, and the total average effective fluence was 30 J/cm². The results showed no significant difference between the groups after three months of treatment: complete lesion response was 76.9% in the MAL 16% group and 79.5% in the MAL 8% group. A linear association was observed between the increase in light dose and a better response in all participants. However, among the 26 participants who received a total effective dose greater than 8J/cm², no relationship was found between an increment in response and an increase in the total dose.

Braathen et al. (2009) evaluated the effect of incubation time, one hour versus three hours, MAL concentration (8% and 16%), and lesion preparation for actinic keratosis treatment. They conducted a multicenter, open, randomized, parallel-group study with a sample composed of 110 participants with 380 previously untreated lesions on the face and scalp. The lesions were debrided, and MAL cream (8% or 16%) was subsequently applied before red light illumination (570-670 nm; light dose, 75 J/cm²). The participants were followed for two to three months. Sixty participants (54%) were retreated and evaluated at six months. The results showed that the overall complete response (CR) rates (after 1 or 2 PDT treatments) were slightly higher after PDT using a 3-hour incubation with MAL 16% compared to other regimens (85% vs. 76% with 1 hour, 16%; 74% with 1 hour, MAL 8%; and 77% with three hours, MAL 8%). For lesions on the face/scalp, CR rates were maintained across all severity ranges (thin, moderate, and thick lesions) after treatment with 1-hour MAL 16% (CR rates ranging from 74 to 86%) or 3 hours MAL 16% (87–96%). The lesion recurrence rates at 12 months after two treatments were similar (19% with one hour vs. 17% with three hours with MAL 16%) and lower for MAL 8% (44-45%).

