**3.5. Randomization**

To randomly assign participants to the experimental groups, a random draw of 144 numbers will be conducted using the website <https://www.sealedenvelope.com/>. The group distribution will be identical (1:1:1:1) for the four groups. The distribution will be carried out in blocks (24 blocks of 6 participants). Opaque envelopes will be labeled with sequential numbers, and inside each envelope will be information regarding the corresponding experimental group, according to the order obtained in the draw. The envelopes will be sealed and will remain unopened in numerical order until the time of lesion treatment. The draw and preparation of the envelopes will be performed by an individual not involved in the study. Immediately before the treatment of the lesions, the investigator responsible for the treatment will open the envelope (without altering the numerical sequence) and will proceed with the indicated procedure.

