**3.10. Study Outcomes**

The primary outcome variable of the study will be:

**• Complete remission** - Quantitative assessment: a count of lesions with a complete response will be performed, meaning those that show total disappearance after treatment. These lesions will be clinically evaluated at 30 days, 3, 6, and 12 months post-treatment, and the number of lesions at these time points will be compared to the baseline. Both absolute and relative lesion counts will be considered. To avoid variability in counting, only one researcher will conduct the counts. This researcher will be calibrated before the study begins. Complete lesion remission will be defined as 100% remission of lesions after 12 months of treatment, as Jansen et al. (2019) described.

The secondary outcome variables will be:

• **Treatment success** - Evaluation of the proportion of participants who show at least a 75% reduction in the initial number of actinic keratosis lesions in the treatment area after the last day. Assessments will be conducted at 30 days, 3, 6, and 12 months. Both absolute and relative lesion counts will be considered. Treatment success will be defined as complete remission in at least 75% of participants over 12 months, as Jansen et al. (2019) established.

**• Recurrence rate** - The recurrence rate of actinic keratoses will be defined as the reappearance of lesions in previously treated areas. Recurrence will be evaluated at the same follow-up periods, namely 30 days, 3, 6, and 12 months after treatment completion. Recurring lesions will be quantified, considering both absolute and relative numbers of lesions. These lesions will be monitored and re-treated at the end of the study unless malignancy is present, in which case they will be treated immediately.

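### Section 3.1 claims 80% power for differences between groups, but its inputs show it only for one unadjusted comparison of the two extreme lesion rates with nobody lost

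*Protocol*

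**What the plan says.** Protocol section 3.1 takes from a cited study of incubation times "complete lesion response rates ranging from 64% to 91% after 3 months" across the four regimens (8% and 16%, each at 1 and 3 hours). It concludes that "with a 95% confidence level and 80% power to detect differences between groups, the minimum sample size will be 36 participants per group". The whole trial is thus put at 144. On the method it adds only: "This result was obtained using a chi-square test for differences in proportions". It does not say which regimen has which rate, or whether the test compares two groups or four.

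Section 3.5 states "The group distribution will be identical (1:1:1:1) for the four groups" and that "a random draw of 144 numbers will be conducted". Since 144 = 4 × 36, nothing is added for loss.

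Section 3.10 sets the primary outcome: "Complete lesion remission will be defined as 100% remission of lesions after 12 months of treatment". The Abstract also says 12 months, while section 2.2 places the primary objective at 3 months. Section 3.4 requires at least five lesions per participant.

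The Contextualization section describes what appears to be the same study (the year is cited differently) and gives closer overall complete response rates, after one or two treatments: "85% vs. 76% with 1 hour, 16%; 74% with 1 hour, MAL 8%; and 77% with three hours, MAL 8"%, where the 85% belongs to 16% with 3 hours.

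**The concern.** The power is claimed for differences between groups in general, but 36 per group is what a two-group calculation on the two extreme rates gives. No other contrast within that range can be larger, and most would be smaller. The rates describe lesions at 3 months, whereas the outcome is total remission and may be judged at 12 months. The number randomised equals the number called the minimum, so any loss takes the trial below it.

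At stake is how a non-significant result will be read. The Justification section presents a lower concentration as potentially cheaper and better tolerated, and the three-hour incubation as a deterrent. If the report cites 80% power, a non-significant difference from G1 could be taken as showing that the lighter regimen works as well.

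**Working it through.** **Inputs.** From section 3.1: p₁ = 0.64, p₂ = 0.91, n = 36 per group, 80% power, 95% confidence (taken as two-sided α = 0.05; the protocol does not state sidedness), chi-square test. From section 3.5: four equal groups. From Contextualization: 0.85, 0.76, 0.74, 0.77. Assumed here because the protocol gives no figures: the middle-group rates, and losses of 10% and 20%.

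**1. The protocol's own figure.** With p̄ = (0.64 + 0.91)/2 = 0.775:

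- n = [1.960·√(2·0.775·0.225) + 0.842·√(0.64·0.36 + 0.91·0.09)]² / 0.27² = (1.157 + 0.470)² / 0.0729 ≈ 36.3, or 37 when rounded up.
- At n = 36: z = (0.27·√36 − 1.157)/0.559 = 0.828, so power = 79.6%.

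So 36 is reproduced within rounding, as a two-group calculation with complete follow-up and no adjustment.

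**2. Four-group chi-square (3 df) on the same extremes, n = 36.** Noncentrality λ = n·Σ(pᵢ − p̄)²/[p̄(1 − p̄)].

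| Assumed rates (%) | Σ(pᵢ − p̄)² | λ | Power | Simulated |
|---|---|---|---|---|
| 64 / 77.5 / 77.5 / 91 | 0.03645 | 7.53 | 62% | 64% |
| 64 / 73 / 82 / 91 | 0.04050 | 8.36 | 68% | 69% |
| 64 / 64 / 64 / 91 | 0.05468 | 9.51 | 74% | 81% |
| 64 / 91 / 91 / 91 | 0.05468 | 14.83 | 91% | 88% |
| 64 / 64 / 91 / 91 | 0.07290 | 15.05 | 92% | 94% |

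The first row is essentially the least favourable case: varying both middle rates between the extremes lowers the approximate power only to 61%, with both near 75%. For 80% power, the first row would need 53 per group and the second 47.

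**3. Loss (assumed), extreme pair, unadjusted.**

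- 10% lost: 36 × 0.9 = 32.4 evaluable per group, power 75%.
- 20% lost: 36 × 0.8 = 28.8 evaluable per group, power 70%.

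**4. Sensitivity check with the Contextualization rates, n = 36.**

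- Four groups: p̄ = 0.78, Σ(pᵢ − p̄)² = 0.0070, λ = 36 × 0.0070/0.1716 = 1.47, power about 15%.
- G1 at 85% against 76%: 16%. Against 74%: 21%. Against 77%: 14%.

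These rates follow one or two treatments, whereas Table 1 in section 3.9.1.1 gives one session, so they are not like for like.

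**5. Unit of the endpoint (illustration only).** If a participant had exactly five independent lesions, the chance of total remission would be p⁵.

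- Section 3.1 rates: 0.64⁵ = 0.107 and 0.91⁵ = 0.624. Power for that pair exceeds 99%.
- Contextualization rates: 0.444 against 0.254, 0.222 and 0.271. Power is 33–52% per comparison with G1, and 45% for four groups.

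Both the number of lesions and their independence are assumptions. The result depends on which lesion rates are put in.

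**The case against.** The strongest reply is that the 80% may well hold for the four-group test. Section 3.1 leaves the middle rates open, and if concentration alone drove response (64/64/91/91) the power would be about 92%. That stands. It rules out saying that 80% is attained only for one pair, and it rules out quoting 62% as the power of the four-group test. It does not supply the missing middle rates.

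A reader might also infer that moving from lesions to participants shows the trial to be underpowered. The documents do not support this. They give no participant-level remission rates, and in the illustration above the conversion raises power on either set of lesion rates. Section 3.10 also describes the outcome through counts of cleared lesions, so the unit is not cleanly fixed, and the 3-month reading in section 2.2 matches the timing of the sizing rates.

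The 85/76/74/77% figures likewise cannot be taken as the rates to expect after one session. Why they are closer together than the 64–91% range cannot be settled without the cited source.

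A multiplicity rule and the handling of missing data may sit in a statistical analysis plan that is not shown, so their absence is not held against the protocol. The loss rates used here are assumptions.

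Nor would resting the power on the two main effects (72 v 72) be a ready rescue. If G1 and G4 were the extremes and both middle groups were at 77.5%, each main effect would compare (91 + 77.5)/2 = 84.25% with (77.5 + 64)/2 = 70.75%, with 49% power.

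**Conclusion.** The power statement is wrong as written because it claims more than its inputs show. They show about 80% for one unadjusted comparison of 64% with 91% and 36 evaluable per group. For the four-group test on the same extremes, power runs from about 62% to about 92%, depending on middle rates the protocol does not give. It is 62–68% when the middle groups are both at the midpoint or equally spaced. For the extreme pair it is 75% or 70% after an assumed 10% or 20% loss. On the closer Contextualization rates, used only as a sensitivity check, it is about 15% overall and 14–21% for each comparison with G1.

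For the primary outcome of 100% remission, power is undocumented and may lie on either side of 80%. The conclusion is that 80% has not been established for the comparison and endpoint planned, not that the trial has been shown to lack it. All figures assume two-sided 5% testing.

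**What to change.** Rewrite section 3.1 so that it:

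- says that 36 per group gives about 80% power for a single unadjusted comparison of 64% with 91%, with 36 evaluable per group;
- gives the power of the four-group test as a range, each value beside its assumed middle rates (for example 62% at 64/77.5/77.5/91, 68% at 64/73/82/91, 92% at 64/64/91/91);
- names the target contrast, the unit (lesion or participant) and the time point, in line with the primary outcome once sections 2.2 and 3.10 are reconciled, and states the rates assumed for that endpoint;
- states the power left under a declared loss, for example 75% at 10% and 70% at 20% for the extreme pair;
- does not claim 80% for the other pairwise contrasts, and says that a non-significant difference will not be read as equivalence.

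This is one rewritten paragraph and needs no increase in enrolment. The cost is a less favourable stated power, and the investigators must commit to assumptions they have so far left open.

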**3.2. Calibration and Training of Evaluators**

After approval by the Research Ethics Committee, the calibration phase will begin. Participants included in the research will be invited to participate in this specific part of the study. After receiving verbal and written explanations, those who agree to participate will sign a specific Informed Consent Form for calibration. The principal investigator (dermatologist) will collect all the study outcomes, and therefore, only this investigator will undergo calibration. He will evaluate 5 participants with actinic keratosis lesions on the face. Each of these 5 participants will be evaluated (T0), and the lesions will be quantified. The 5 participants will be seen in sequence and reassessed after 1 hour. The same evaluation (lesion recount) will be performed (T1), and the results will be recorded. The Intraclass Correlation Coefficient (ICC) will be calculated to assess the intra-examiner agreement between T0 and T1 values. A value of ≥ 0.80 will be considered adequate regarding the agreement on the number of lesions. These procedures are important to maximize the reproducibility of the evaluations. These participants will receive dermatological treatment for actinic keratoses as needed. These assessments will not be part of the study but will confirm the intra-examiner agreement.

## **3.3. Sample Description**

## The sample will consist of individuals with photodamaged skin affected by multiple actinic keratoses on the face, classified as grade I (thin), grade II (moderately thick), or grade III (thick), as defined by Olsen et al. (1991).

**3.4. 3.4. Inclusion and Exclusion Criteria**

The study will include individuals:

• of both sexes,

• aged between 40 and 80 years,

• with Fitzpatrick skin phototypes I to IV,

• with photodamaged skin presenting at least five clinically evident actinic keratosis lesions on the face to be treated,

• who have had no previous treatment for at least six months.

The study will exclude individuals with:

• clinically diagnosed infiltrative lesions, as the gold standard treatment is surgical with histopathological evaluation of the lesion (surgery will be performed at no cost to the participant), and they will receive guidance and referral for appropriate treatment,

• photosensitive diseases such as systemic lupus erythematosus, dermatomyositis, and porphyria, among others,

• clinically diagnosed malignant lesions (any type of skin cancer); those suspected during dermatoscopy at the time of the initial lesion count will be referred for surgical treatment through the Brazilian Unified Health System (SUS),

• a history of arsenic exposure,

• known allergy to MAL or similar photosensitizing agents,

• psychoactive drug abuse,

• prior radiation therapy at the lesion site(s),

• participation in another clinical study,

• intense tanning at the time of treatment,

• pregnant or breastfeeding women,

• local or systemic infection,

• immunosuppression, uncompensated chronic diseases, or emotional disorders considered contraindications for treatment,

• skin conditions on the neck and anterior chest region.

**3.5. Randomization**

To randomly assign participants to the experimental groups, a random draw of 144 numbers will be conducted using the website <https://www.sealedenvelope.com/>. The group distribution will be identical (1:1:1:1) for the four groups. The distribution will be carried out in blocks (24 blocks of 6 participants). Opaque envelopes will be labeled with sequential numbers, and inside each envelope will be information regarding the corresponding experimental group, according to the order obtained in the draw. The envelopes will be sealed and will remain unopened in numerical order until the time of lesion treatment. The draw and preparation of the envelopes will be performed by an individual not involved in the study. Immediately before the treatment of the lesions, the investigator responsible for the treatment will open the envelope (without altering the numerical sequence) and will proceed with the indicated procedure.

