## **3. MATERIAL AND METHODS**

## This is a single-center, controlled, randomized, parallel-group, prospective clinical trial, following the criteria outlined in the SPIRIT Statement clinical protocol. The project will be submitted to the Research Ethics Committee of Universidade Nove de Julho (UNINOVE). After approval, individuals waiting for medical and dental care at the outpatient clinics of Universidade Nove de Julho will be individually invited by the principal investigator to participate in the study. Additionally, patients who attend the principal investigator's private practice, Perfecthaderm Medical Clinic, located at [name], will also be invited to participate in the study.

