## Participants who meet the study's inclusion criteria will be invited to attend the clinical outpatient clinic at UNINOVE, São Paulo, Brazil, to receive dermatological treatment from the dermatologist (principal investigator) between March 2024 and October 2024 (end of treatments). The final one-year follow-up will occur in October 2025. Those who agree to participate will sign the Informed Consent Form (ICF) after a detailed verbal and written explanation provided by the principal investigator.

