**3.7. Avaliações pré-tratamento**

After receiving the necessary explanations, participants affected by actinic keratosis who sign the Informed Consent Form (ICF) will undergo anamnesis and complete the AKQoL and Face-Q questionnaires, as well as the data collection form for the study, which will involve counting, classifying, and mapping the facial lesions. These data will be collected by the principal investigator (calibrated). Photographic records of the lesions will also be taken using a Quantificare® 3D camera and the camera of an iPhone 11 Pro Max. Following these evaluations, the treatment will be conducted according to the randomization.

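### The protocol prints one fixed block size of six and contradicts itself on whether the investigator who recruits also opens the envelopes, so some assignments may be predictable

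*Protocol*

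**What the plan says.** Section 3.5 sets the ratio ("The group distribution will be identical (1:1:1:1) for the four groups") and the block structure ("The distribution will be carried out in blocks (24 blocks of 6 participants"). Envelopes are opaque, sealed and numbered. On their preparation: "The draw and preparation of the envelopes will be performed by an individual not involved in the study". Just before treatment, "the investigator responsible for the treatment will open the envelope (without altering the numerical sequence) and will proceed with the indicated procedure".

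The roles are described in several places:
- Section 3, recruitment: patients from the university clinics "will be individually invited by the principal investigator to participate in the study"; patients of that investigator's private practice are invited too.
- Section 3, timetable: participants attend "to receive dermatological treatment from the dermatologist (principal investigator) between March 2024 and October 2024".
- Section 3.2: the principal investigator collects all outcomes and is the only person calibrated.
- Section 3.7, on the baseline count, grading and map: "These data will be collected by the principal investigator (calibrated".
- Section 3.6: only the treating investigator knows the assignments, and the investigator responsible for data collection is blinded.

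**The concern.** Sealed envelopes hide each assignment taken singly. They do not stop inference from a constant block length combined with assignments already made. The protocol prints the length, and the person who opens envelopes in order sees every past assignment.

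It matters whether that person also recruits. Patients come from two streams under one recruiter. Some eligibility criteria call for judgement, such as clinically evident lesions and intense tanning. The baseline lesion count is the reference for remission, for the 75% reduction and for the relative counts. Someone who could anticipate the next arm could, without intending to, influence who is enrolled next or how that patient's lesions are counted. Resulting differences between arms could not be reliably removed in the analysis.

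**Working it through.** **The plan's own figures.** 24 × 6 = 144 and 144 / 4 = 36, so the totals agree. Within a block, 6 / 4 = 1.5 per arm, so no block can be balanced. The nearest feasible make-up is two arms twice and two arms once (2:2:1:1). If each arm is doubled in 12 of the 24 blocks, it receives 12 × 2 + 12 × 1 = 36. This make-up is an assumption; the protocol states none.

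**Set-up.** The guesser knows the block length and all earlier assignments in the block, and always names the likeliest next arm. All orders within a block are equally likely, and blocks are treated as independent. Chance is 25% for the arm and 50% for incubation time. The probabilities by position come from exact enumeration.

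**Case A: the recruiter treats; which arms are doubled is random and unknown.**
- The sixth assignment is certain only when it is one of the two single arms, because that arm is then missing from the first five. The probability is 2/6 = 1/3.
- Share certain: (1/3) / 6 = 5.6%, or 8 of 144.
- Best guess correct by position: 0.250, 0.289, 0.344, 0.433, 0.500, 0.556. The sum is 2.372, and 2.372 / 6 = 39.5%.

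**Case B: the recruiter treats; the make-up of each block is known.**
- The sixth is always certain. The fifth is certain when both copies of a doubled arm remain: 2 × 1/15 = 0.133.
- Share certain: 1.133 / 6 = 18.9%.
- Best guess correct by position: 0.333, 0.400, 0.433, 0.467, 0.567, 1.000. The sum is 3.200, and 3.200 / 6 = 53.3%.

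**Case C: someone else treats; the recruiter sees only whether past dressings stayed on for 1 or 3 hours; doubled arms unknown.**
- The two doubled arms share an incubation time with probability 2/6 = 1/3, giving a 4:2 block; otherwise the block is 3:3.
- Certainty arises only in 4:2 blocks. The sixth is certain if it has the rarer time (2/6), and the fifth if the first four all have the commoner time (1/15). That is 1/3 × (2/6 + 1/15) = 1/3 × 0.4 = 0.133 per block, and 0.133 / 6 = 2.2%.
- Best guess correct by position: 0.500, 0.578, 0.578, 0.644, 0.644, 0.778. The sum is 3.722, and 3.722 / 6 = 62.0%.
- If the make-up were known, the sixth incubation time would always be certain, so the share would be at least 1/6 = 16.7%.

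**Alternatives, guessing the arm with all past assignments known.**

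| List | Certain | Best guess correct |
|---|---|---|
| Blocks of 6, doubled arms unknown | 5.6% | 39.5% |
| Blocks of 6, make-up known | 18.9% | 53.3% |
| Fixed blocks of 4 | 25.0% | 52.1% |
| Fixed blocks of 8 | 14.3% | 47.0% |
| Fixed blocks of 12 | 10.0% | 44.1% |
| Blocks of 8, 12 and 16 in random order, set of sizes known | about 2.5% to 3.3% | about 43.9% |
| One draw of 144, 36 per arm | 0.9% | 31.5% |

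Check for size 4: (1/4 + 1/3 + 1/2 + 1) / 4 = 52.1%, and the last of every four is certain (36 of 144). The row for varying blocks is simulated, and its certain share depends on how much the guesser knows about the set.

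**The case against.** The strongest reply is that sections 3.2, 3.6 and 3.7, read together, make the principal investigator the blinded data collector. Only one phrase in section 3 has this person treating, and it may be loose wording. If so, the recruiter opens no envelope and Cases A and B fall away. That stands as a possible reading, so it is not settled that the recruiter knows past assignments. The phrase is nevertheless in the protocol, and nothing else names the treating investigator.

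Case C is also only a possibility. No section places the recruiter where dressing times can be seen, and section 3.9.1.1 lets participants go home during incubation.

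The safeguards in section 3.5 are genuine: opaque, sealed, sequential envelopes prepared by an outsider. Sections 3.5 and 3.7 already put the baseline count before that patient's own envelope is opened. This protects the count from the opened assignment, but not from inference based on earlier ones.

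A reader might infer that upcoming assignments can in general be worked out. The figures do not support this: about 6% to 19% would be certain in Cases A and B, under a make-up the protocol never gives. A reader might also infer that selection bias would be undetectable. That goes too far, because the baseline counts, grades, maps and photographs allow some comparison between arms.

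**Conclusion.** The point holds as a weakness in concealment together with a contradiction over roles. It is not evidence that allocation is open. Two things are certain from the text: one constant short block length is printed, and the statements on who treats cannot all be true.

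The size depends on how the contradiction resolves. If the recruiter treats, 5.6% of assignments are certain and 39.5% correctly guessed, rising to 18.9% and 53.3% if the block make-up is known (chance 25%). If another person treats and dressing times are visible, the figures for incubation time are 2.2% and 62.0% (chance 50%). All rest on the assumed 2:2:1:1 make-up and on a guesser who uses every past assignment; real foreknowledge would probably be less.

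The divisibility error means the list must be regenerated anyway. The obvious repair, a fixed block of four, would raise the certain share to 25%. The change is worth making because it is cheap.

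**What to change.** 1. In section 3.5, replace the blocks of six with one random draw of 144 containing exactly 36 per arm. This suits a single-centre trial with no stated strata, and the section already speaks of drawing 144 numbers. The alternative is blocks of randomly varying size, each a multiple of four, for example four each of 8, 12 and 16: 4 × (8 + 12 + 16) = 144. The sizes should be held only by the uninvolved person who prepares the envelopes and kept out of the protocol given to the team. The single draw is preferable: if the set of sizes became known, varying blocks would allow about 43.9% correct guesses, more than the 39.5% of Case A, although fewer assignments would be certain. Do not simply change the block to a fixed four.

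2. Reconcile the timetable paragraph of section 3 with sections 3.2, 3.6 and 3.7, so that the person who opens envelopes and treats is not the person who recruits and counts lesions.

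The cost is a sentence in section 3.5, a correction in section 3, and a new list from the same outside person using the same envelope system. Balance between arms over the March to October 2024 treatment period becomes slightly looser. If recruitment has begun, only the unused envelopes need replacing, with a list that completes each arm to 36.
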